### Cost and Cost-effectiveness of Measures

Both financial and time costs for participants to use each of the methods will be assessed. The time spent by researchers and participants in the administration of each 24HR method will be recorded for each participant. This includes time spent training individuals to take the mFR24 images, time spent completing the 24HR interview, and any time spent supporting individuals to complete their 24HR interviews. The time spent by researchers coding the mFR24 data will also be recorded. Both ASA24 and Intake24 have the capability to collect time stamp data to identify how much time the participants spend inputting data. All other time data, including time spent cleaning the data, will be manually collected by researchers.

Financial costs, such as server space for digital data storage, will be recorded. After converting the time data to a financial cost, the total cost data will be considered in parallel with the measures of accuracy derived for the 3 methods. The primary accuracy measure for cost-effectiveness is the absolute percentage error in energy intake. Comparing costs with accuracy will identify whether any of the 3 methods are dominated by another (ie, is more expensive and less accurate). If not, the cost per person to reduce absolute misreporting by 1% point will be estimated.

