#### Cost-effectiveness

Both participant and researcher time costs will be multiplied by standard staff costs (including on-costs) to estimate the financial cost of using each method on a per-person basis. Differences in time cost and total financial cost will be compared across methods using a repeated measures analysis of variance test. P<.05 will be considered statistically significant. If statistically significant differences exist, differences in cost-effectiveness will be assessed using the same procedure. Cost-effectiveness will be defined as the cost per person to reduce the absolute misestimation of energy intake by 1% point.

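### The rule for reporting the cost of a 1-point reduction in energy error does not cover the two methods left when one of three is dominated, and its condition differs between two sections

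*Protocol article*

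**What the plan says.** Two sections of the protocol article govern this outcome.

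**Cost and Cost-effectiveness of Measures.** The accuracy input is fixed: "The primary accuracy measure for cost-effectiveness is the absolute percentage error in energy intake". The dominance check follows: "Comparing costs with accuracy will identify whether any of the 3 methods are dominated by another (ie, is more expensive and less accurate". The next sentence sets the condition for the ratio: "If not, the cost per person to reduce absolute misreporting by 1% point will be estimated".

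**Data Analyses, Cost-effectiveness.** Costs are tested first: "Differences in time cost and total financial cost will be compared across methods using a repeated measures analysis of variance test", at the 5% level. Then: "If statistically significant differences exist, differences in cost-effectiveness will be assessed using the same procedure". The outcome is defined as the same ratio: "Cost-effectiveness will be defined as the cost per person to reduce the absolute misestimation of energy intake by 1% point". This subsection does not mention dominance.

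**The concern.** With two methods, the sequence in the measures section is complete. If one dominates, the choice is settled; if neither does, the ratio expresses the trade-off. With three methods it is not complete. Dominance removes only the dominated method, and the other two may still trade cost against accuracy. In the sentence as written, *If not* refers back to whether any of the three is dominated, so the case of one dominated and two remaining has no stated rule.

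The case is plausible here. ASA24 and Intake24 are both self-administered web tools built on the same Australian food composition tables, with similar completion times in earlier work (17 to 34 minutes, and 20 minutes on average). The mFR24 adds participant training, a trained interviewer and researcher coding. If mFR24 proved both the costliest and the most accurate, whether any method counted as dominated would depend only on how the two web tools ranked against each other, and that gap could be small.

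Cost-effectiveness is in the title and the first objective, and the Strengths and Limitations section presents its evaluation as what makes the study unique. At stake is whether the ratio that survey planners would use is reported under a rule fixed in advance or one chosen after the results are seen.

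**Working it through.** The protocol gives no cost or error figures, so there is no stated number to reproduce. The check has three parts.

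**1. Count the orderings.** Number the methods by cost, 1 < 2 < 3, without ties. Give each an error rank (1 = most accurate). A method is dominated if a cheaper one has lower error. There are 3! = 6 orderings:

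| Error ranks of methods 1, 2, 3 | Dominated | Remaining | Ratio defined among those remaining? | Covered by the plain reading? |
|---|---|---|---|---|
| 1, 2, 3 | 2 and 3 | 1 | Not needed | – |
| 1, 3, 2 | 2 and 3 | 1 | Not needed | – |
| 2, 1, 3 | 3 | 1, 2 | Yes | No |
| 2, 3, 1 | 2 | 1, 3 | Yes | No |
| 3, 1, 2 | 3 | 1, 2 | Yes | No |
| 3, 2, 1 | none | 1, 2, 3 | Yes | Yes |

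A ratio exists among undominated methods in 3 + 1 = 4 of 6 orderings. The plain reading covers 1 of those 4 and leaves 3 without a rule.

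**2. Illustrate one uncovered case.** Assumed values (cost units, absolute % error): A (20, 20), B (30, 22), C (60, 15). A dominates B, because B costs 10 more and errs 2 points more.

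- A to C: (60 − 20)/(20 − 15) = 40/5 = 8 cost units per point. This ratio is defined and is the one a planner needs.
- B to C: (60 − 30)/(22 − 15) = 30/7 ≈ 4.3 cost units per point. It makes C look cheaper per point only because the comparator is a method nobody should choose.
- A to B: (30 − 20)/(20 − 22) = 10/(−2) = −5. This has no meaning as the price of an improvement.

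So it matters both whether a ratio is reported and which methods it compares.

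**3. Set the two conditions side by side.**

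| Result | Measures section | Cost-effectiveness subsection |
|---|---|---|
| None dominated, costs differ significantly | Ratio promised | Ratio compared |
| None dominated, costs do not differ significantly | Ratio promised | Condition not met |
| One dominated, costs differ significantly | No rule for the two left | Ratio compared; methods not specified |
| One dominated, costs do not differ significantly | No rule for the two left | Condition not met |

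The sections agree on providing for the ratio in the first row only. In the second and third rows, one section provides for it and the other does not. In the fourth, neither does.

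**The case against.** A reader might infer that a single dominated method cancels the cost-effectiveness result for the other two. The documents do not support that. The sentence says *if*, not *only if*, and nowhere states that the ratio is withheld. It can also be read method by method: dominance is a relation between one method and another, so the sentence may mean that the ratio is estimated for whichever methods are not dominated, which is ordinary practice. The later subsection also provides for the same ratio with no dominance condition, so under significant cost differences a comparison would still be made. All of this stands, and it limits the point to an incomplete rule with an unmatched condition.

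It can also be argued that the two sections do different jobs, one governing estimation and the other a test of differences. That could explain the second row of the side-by-side table. It does not resolve the third, where a comparison is planned on ratios that the other section has not promised and with no statement of which methods enter. The later subsection therefore does not cure the gap.

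Two further objections hold in part. The ordering counts say nothing about likelihood and take the plain reading as given, so they cannot prove that reading. And extended dominance is detail that an article may leave to a fuller plan. Its absence is not the fault here; it appears in the fix only because a complete rule for three methods needs it.

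**Conclusion.** The point holds as a minor correction. Read plainly, the measures section promises the ratio only when none of the three methods is dominated, and it is silent on the two that remain when exactly one is. That is 3 of the 6 orderings, and 3 of the 4 in which a ratio exists among undominated methods. The Cost-effectiveness subsection sets a different condition for the same outcome. Two analysts following the document could report different results from the same data.

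The counts assume no ties and the plain reading of the sentence. They are not probabilities, and the protocol offers no figures from which to derive any. The stronger inference, that the result for the remaining methods is lost, is not supported: times, financial costs and energy intakes are all to be collected, so every pairwise ratio stays computable. The accuracy and acceptability analyses are not affected.

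**What to change.** In Cost and Cost-effectiveness of Measures, replace the *If not* sentence with:

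> Any dominated method (including by extended dominance) will be removed, and the incremental cost per person per 1-percentage-point reduction in absolute energy error will be estimated between adjacent remaining methods ordered by cost.

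Extended dominance means that a method is also removed if its ratio against the next cheaper remaining method is higher than the ratio of the next costlier remaining method against it. If only one method remains, it is reported as dominating the others and no ratio is given.

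In Data Analyses, Cost-effectiveness, state that the ratio is reported under this same rule, so that reporting it no longer depends on a significant cost difference. Changing the measures section alone would leave the two conditions unmatched.

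The cost is one sentence in each section. It needs no new data and no change to trial conduct.

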### Data Analyses

#### Energy Intake Estimation Accuracy

The participant feeding days with at least two meals eaten at the food laboratory will be included in the analyses. Daily energy intake from each 24HR method and the controlled feeding sessions will be calculated, excluding any items reportedly consumed outside of the food laboratory. Outlier checks will be conducted to identify any obvious keying errors or food composition data anomalies, which will be corrected before proceeding. Bland-Altman plots will be used to test for agreement between the 24HR values and controlled feeding measures at the individual and group levels. Repeated measurements will be analyzed using the linear mixed models procedure using SPSS version 25, accounting for age, gender, and BMI, with 24HR method and method order as fixed effects, to assess whether there are statistically significant differences by 24HR method. Misreporting will be assessed by examining the ratio of reported 24HR intake to observed intake, with the lowest tertile considered to indicate underreporting. The proportion of underreporters in each 24HR method will be compared using chi-square tests and logistic regression. Among underreporters, the total energy misestimation will also be compared using regression models adjusted for age, gender, and BMI.

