## Methods

### Sample and Recruitment

The sample will be selected from adults aged 18-70 years residing in Perth, the capital city of Western Australia, Australia, and recruited via the electoral roll by selecting postcodes that provide representation across socioeconomic status. Other recruitment methods will include advertising on the Curtin University website and a snowball methodology (eg, email newsletter and referrals from friends or colleagues). A final sample of 150 randomized participants (allowing for a 20% dropout) will allow for 90% power at a 5% significance level when the true difference between any 2 mean differences between estimated and observed dietary energy intake is 0. Quota sampling will be used to ensure that equal numbers of men and women are recruited. To be included in the study, participants must be able to attend in-person feeding sessions on 3 separate days and have access to a computer and a smartphone (running iPhone operating system or Android operating system) with a data plan. Exclusion criteria include serious illnesses or medical conditions, pregnancy, special dietary requirements, or dietary restrictions because of food allergies or intolerances or dieting to lose weight.

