### Study Design

A controlled feeding study with a crossover design will compare the accuracy of 3 technology-assisted methods of assessing 1 day of dietary intake: ASA24, Intake24, and mFR24. The sequence of the 3 dietary assessment periods will be randomized for each participant, with a 1-week washout period between each feeding session (Figure 1). Therefore, each participant will be exposed to each of the 3 methods at different periods. The crossover design, a repeated measurement design, will allow both between-group and within-group method comparisons. This design yields a more efficient comparison of treatments than a parallel design because fewer participants are required in the crossover design to attain the same level of statistical power or precision as a parallel design.

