#### Correlates of Energy Misestimation

Psychosocial, demographic, and cognitive factors associated with omission and intrusion rates and with energy misestimation on each 24HR method will be evaluated using chi-square tests and multivariate logistic regression. The effects of factors will be reported as odds ratios and associated 95% CIs. Some dietary factors in the Accuracy and Cost-effectiveness of Technology-Assisted Dietary Assessment study are standardized because of the controlled feeding methodology (meal frequency and eating location), but it is hypothesized that food and meal complexity and physical form will affect reporting accuracy via an interaction with cognitive factors. P<.05 will be considered statistically significant in all analyses.

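### Underreporting is defined as the lowest tertile of the reported/observed ratio, so one third of recalls carry the label whatever the accuracy, and comparing its frequency between methods shows relative rank at most

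*Protocol article*

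**What the plan says.** All the relevant text is in the protocol article, Data Analyses, Energy Intake Estimation Accuracy.

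- Measure: "Misreporting will be assessed by examining the ratio of reported 24HR intake to observed intake".
- Label: "with the lowest tertile considered to indicate underreporting".
- First use: "The proportion of underreporters in each 24HR method will be compared using chi-square tests and logistic regression".
- Second use: "Among underreporters, the total energy misestimation will also be compared using regression models adjusted for age, gender, and BMI".

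The section does not say whether the tertile is formed within each method or over all recalls together. No absolute limit on the ratio appears anywhere in the article. The Study Design section makes this a crossover in which "each participant will be exposed to each of the 3 methods at different periods", so each method supplies about the same number of recalls from the same people.

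**The concern.** A tertile is a share of the sample. Once underreporting means being in the lowest third, its overall frequency is set before any data are seen and carries no information about how much underreporting occurred. The plan then treats that frequency as an outcome and tests it between methods.

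This matters because the study has a true reference. Intake is weighed at the food laboratory, so a ratio of 1 means accurate reporting, and a cut that floats with the sample discards that anchor. A published proportion of underreporters per method would be read as a prevalence by those choosing a method for dietary surveillance, and it would not be one. The same label also selects the recalls for the regression of energy misestimation among underreporters.

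**Working it through.** **The plan's own figures.** The article gives no expected proportion of underreporters, so there is none to reproduce. For the number of recalls, the Sample and Recruitment section says: "A final sample of 150 randomized participants (allowing for a 20% dropout) will allow for 90% power at a 5% significance level". With 20% dropout, 150 × 0.80 = 120 completers, or 120 × 3 = 360 recalls. The argument does not depend on these counts; they only make it concrete.

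**Reading A: tertile within each method.** Each method has 40/120 = 33.3% underreporters. The 2 × 3 table is 40/40/40 against 80/80/80, so chi-square = 0 and every unadjusted odds ratio is 1. A simulation of 120 completers (2,000 replicates; lognormal ratios, log SD 0.20 and within-person correlation 0.4, all assumed) rejected in 0% of replicates, even with median ratios of 0.75, 0.95 and 1.05.

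**Reading B: tertile on the pooled recalls.** The overall share is 120/360 = 33.3% by construction.

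*Step 1, all methods equally accurate.* Assume a lognormal ratio with log SD 0.25 (an assumption; the article gives no SD).

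- Cut = median × exp(0.25 × z(1/3)), with z(1/3) = −0.431, so cut = median × 0.898.
- Share below 0.90 = Φ(ln(0.90/median)/0.25). The value 0.90 is an illustrative fixed limit, not a figure from the article.

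| Median ratio, all methods | Tertile cut | Labelled | Below 0.90 |
|---|---|---|---|
| 0.80 | 0.718 | 33% | Φ(0.471) = 68% |
| 1.00 | 0.898 | 33% | Φ(−0.421) = 34% |
| 1.20 | 1.08 | 33% | Φ(−1.151) = 12.5% |

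In the last row, the share with a ratio below 1 is Φ(ln(1/1.20)/0.25) = Φ(−0.729) = 23.3%. So 33.3 − 23.3 = 10.0% of all recalls are labelled underreporting although energy was over-reported. That is 10.0/33.3 = 30% of those labelled, and they would enter the analysis among underreporters.

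*Step 2, methods differ.* Same simulation as under Reading A (log SD 0.20):

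| Median ratios | Pooled cut | Labelled, by method | Below 0.90, by method |
|---|---|---|---|
| 0.8 / 0.9 / 1.0 | 0.81 | 54% / 31% / 15% | 72% / 50% / 30% |
| 1.1 / 1.2 / 1.3 | 1.09 | 49% / 32% / 19% | 16% / 8% / 3% |

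The pooled test does detect differences: it rejected in 100% and 99.7% of replicates. The levels, however, are wrong as frequencies of underreporting. A set of methods that all over-report yields much the same pattern of labels as a set in which two of the three under-report. The fixed limit separates the two situations.

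**The case against.** The strongest reply is that the planned comparison makes sense only if the tertile is pooled, that the analysis plan may say so, and that a pooled test is informative. The first aim is to compare methods, and relative position partly serves it. This stands in part. On the pooled reading the test is not empty, and the shares do follow differences between methods. A reader might infer that the comparison is void in every case; the article supports that only for the within-method reading, which it neither states nor rules out. What the reply does not rescue is the label. A statement of how the tertile is formed would not tie it to a ratio below 1.

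Three further inferences are tempting and should not be drawn.

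- **That the main accuracy comparison fails.** The same section compares methods by a linear mixed model and Bland-Altman plots, and the cost-effectiveness sections use absolute error in energy intake. None of these uses the tertile, and the abstract does not mention it.
- **That the odds ratios under Correlates of Energy Misestimation inherit the problem.** That section does not say how its binary outcome is defined, so the article does not show this.
- **That the tertile is worse because it responds to spread as well as bias.** Any one-sided cut does. With two methods at median 1.00 and log SD 0.10 and 0.30, a pooled tertile labels 25% and 41%; a fixed cut at 0.90 labels 14.6% and 36.3%. Spread is no reason to prefer the fixed cut.

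It is also fair to say that limits such as 0.90 have no source in the article.

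**Conclusion.** The point holds for two analyses: the comparison of underreporter proportions between methods, and the regression of energy misestimation among underreporters. The fixed overall share of one third follows from the definition alone and needs no distributional assumption; likewise the 33.3% in every method if tertiles are formed within method (apart from rounding and ties). The sizes under pooling rest on an assumed lognormal ratio with log SD 0.25 or 0.20: 33% labelled where 68% or 12.5% lie below 0.90, with the cut at about 1.08 in the latter case. Other values of the SD would move these figures but would not tie the label to a ratio of 1.

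This is a stated rule that does not measure what it is named for, not a detail left out of a condensed article. It does not touch the study's main accuracy estimates.

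**What to change.** Before analysis starts (the Results section schedules it for 2022):

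1. Replace the tertile with one fixed cut on reported/observed energy, the same for all three methods, with a separate over-reporting category so that over-reporters are not merged with accurate reporters. Limits of 0.90 and 1.10, with 0.80 and 1.20 as a sensitivity analysis, would illustrate the form; the investigators should choose and justify the values.
2. Compare methods on log(reported/observed) as a continuous outcome in the linear mixed model already planned.
3. Use the fixed-cut category to define the set for the analysis among underreporters.
4. If tertiles are kept, state that they are formed on the pooled recalls and call the category lowest relative reporting, not underreporting.

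The cost is wording only, with no new data. The small downside is that any fixed cut is a choice, which the sensitivity cut covers.

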### Strengths and Limitations

This study has several strengths and limitations. A strength of this study is the collection of observed food and beverage intake using a controlled feeding study design. Many criterion validation studies use biomarkers of energy expenditure, which indicate the magnitude of misreporting, but do not help to understand differential misreporting of food and beverage items nor the underlying mechanisms. For example, certain food types may be more frequently omitted from reporting, or certain food portion sizes may be frequently misestimated. Another strength is the crossover design of the study, which allows for between- and within-group comparisons. Few studies have compared 24-hour recall methods with reference methods using a within-group comparison, and those studies did not use technology-based methods [90,91]. Studies assessing multiple technology-based 24HR methods have included different participants completing each method [33,46]. In such studies, between-person differences in dietary intake and recall biases may have contributed to the observed differences. The within-group comparison of the 3 dietary assessment methods in our study will enable a comparison not subject to confounding by between-person variation. This is an important strength of this study, as it will also allow the evaluation of consumer acceptability of these methods. The uniqueness of this study is the evaluation of the cost-effectiveness of the 24HR methods. This will provide valuable data for policy makers and researchers planning large-scale surveys.

A limitation of this protocol study is that the limited number of foods offered may facilitate a better chance of a match between reported and observed intakes than if the study was conducted in a free feeding environment. Another limitation of this study is the self-selecting sample, meaning that the findings may not be fully generalizable to the wider population, as study participants who volunteered may be more motivated to complete dietary assessment methods because of their own interest in dietary intake. Recruitment through the electoral roll is an important aspect of the study design that facilitates a wide and diverse recruitment. In addition, randomization by gender aims to recruit equal proportions of men and women across the groups so that gender differences can be assessed.

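### The underreporter-only comparison of energy misestimation selects recalls on the outcome being compared, so this supplementary analysis mixes bias with spread and loses the within-person contrast

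*Protocol article*

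**What the plan says.** All of the following is in the protocol article. Under Study Design: "The sequence of the 3 dietary assessment periods will be randomized for each participant", so each person uses every method.

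Under Energy Intake Estimation Accuracy, the main comparison is a linear mixed model on the repeated measurements that has age, gender and BMI as covariates and is specified "with 24HR method and method order as fixed effects, to assess whether there are statistically significant differences by 24HR method". The section then turns to misreporting:
- The measure is a ratio: "Misreporting will be assessed by examining the ratio of reported 24HR intake to observed intake". The threshold is relative to the sample rather than a fixed value: "with the lowest tertile considered to indicate underreporting". It does not say whether the tertile is cut on the ratios of all three methods together or within each method.
- The shares below that threshold are tested between methods: "The proportion of underreporters in each 24HR method will be compared using chi-square tests and logistic regression".
- The last step is the analysis at issue here, restricted to the selected recalls: "Among underreporters, the total energy misestimation will also be compared using regression models adjusted for age, gender, and BMI".

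Under Correlates of Energy Misestimation, the 5% significance threshold is applied to every analysis. Nothing labels the underreporter-only comparison as descriptive.

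**The concern.** Underreporter status is read off the ratio of reported to observed energy, a result of using the method. The next step compares energy misestimation, which is the same result in another form, among those selected. Two things follow.

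First, the people who fall in the lowest tertile with one method are largely not those who do so with another, so the within-person contrast that the crossover provides is mostly lost in this analysis. Age, gender and BMI are baseline covariates and cannot remove selection made on the outcome.

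Second, the mean of a lower tail depends on the spread of the distribution as well as on its centre. A method with little average bias but wide scatter can show a worse tail than a method with more bias and little scatter.

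The study is meant to inform the choice of a method for surveillance. A P value below .05 for size of underreporting by method is likely to be quoted, and the reader could not tell whether it reflected bias, spread or selection.

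**Working it through.** The plan gives no figure for this analysis, so there is none to reproduce.

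**Inputs.** From the article: three methods per person, a lowest-tertile cut, and 150 randomized with 20% dropout, so 150 × 0.8 = 120 completers. Assumed, because the documents give none: normally distributed ratios, their means and SDs, and within-person correlations of 0.3 and 0.6. Misestimation is expressed as the ratio. In energy units it is (ratio − 1) × observed intake, and the selection acts in the same way.

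**Formulas.** For a method with mean μ and SD σ and a cut c, let a = (c − μ)/σ.
- Share below the cut: Φ(a).
- Mean ratio among those below: μ − σ φ(a)/Φ(a).
- Pooled tertile: c is the value at which the average of Φ(a) over the three methods is 1/3.
- Within-method tertile: a = −0.431 and φ(a)/Φ(a) = 1.091, so the mean is μ − 1.091σ.
- Whole-sample shortfall E max(0, 1 − ratio): s = (1 − μ)Φ((1 − μ)/σ) + σφ((1 − μ)/σ).
- Whole-sample absolute error E|ratio − 1|: 2s + (μ − 1).

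**Case 1: equal spread.** Means 0.95, 0.85, 0.85; SD 0.15.
- Pooled, c = 0.815. First method: a = −0.900, mean 0.95 − 0.15 × 0.2662/0.1842 = 0.733. Others: a = −0.233, mean 0.85 − 0.15 × 0.3883/0.4079 = 0.707. The true gap of 0.10 becomes 0.026.
- Within method: 0.95 − 0.164 = 0.786 and 0.85 − 0.164 = 0.686. The gap stays at 0.10.

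**Case 2: equal means, unequal spread.** Means all 0.92; SD 0.15, 0.25, 0.20.
- Pooled, c = 0.837: 0.743, 0.665, 0.704. False gap between the first two: 0.078.
- Within method: 0.92 − 1.091 × 0.15 = 0.756; 0.92 − 1.091 × 0.25 = 0.647; 0.92 − 1.091 × 0.20 = 0.702. False gap between the first two: 0.109.

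**Case 3: order on mean bias reversed.** Method A 0.88 (SD 0.15), B 0.95 (SD 0.25), C 1.00 (SD 0.20).

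| | A | B |
|---|---|---|
| True mean ratio | 0.88 | 0.95 |
| Underreporter mean, pooled cut (c = 0.851) | 0.742 | 0.684 |
| Underreporter mean, within-method cut | 0.716 | 0.677 |
| Whole-sample shortfall | 0.138 | 0.127 |
| Whole-sample absolute error | 0.156 | 0.203 |

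A has the larger average bias and the larger shortfall, yet looks better among underreporters. In 4,000 simulated studies of 120 people, the A–B order was reversed in about 100% (pooled) and in 89–93% (within method). The whole-sample means had the right order in about 100%.

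**Case 4: an unbiased but imprecise method.** Means 1.00, 0.88, 0.88; SD 0.25, 0.12, 0.15.
- Pooled, c = 0.836: shares 26%, 36%, 39%; underreporter means 0.69, 0.75, 0.73. The unbiased method has the fewest underreporters but the lowest mean among them.
- Within method: 0.73, 0.75, 0.72. The unbiased method is no longer lowest.
- Whole-sample shortfall: 0.10, 0.13, 0.14. Absolute error: 0.20, 0.14, 0.16.

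**Null check.** With the same mean and SD in all three methods, the simulation showed no false difference under either cut.

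**Overlap.** Across the simulated settings, only 11–26% of people who were underreporters on any method were so on all three.

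**The case against.** The strongest reply is that this analysis is an addition. The methods are compared in the full sample by the mixed model, with Bland-Altman plots, and absolute percentage error is already the accuracy measure for cost-effectiveness. Nothing in the article uses the underreporter result to choose a method. This stands, and it limits the point to one supplementary regression.

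The examples also have limits. Shrinkage appears only with a pooled cut. Reversal needs unequal spread, which the documents neither show nor exclude. In Case 3 (A against B) and in Case 4 with a pooled cut, the subset order matches the order on absolute error, so it is wrong only for mean bias and shortfall. This also stands. It shows that the subset result mixes bias and spread, which separate whole-sample models would tell apart.

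How severe underreporting is among those who underreport is a fair descriptive question. That supports keeping a description, not a between-method test.

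Three stronger readings are tempting but unsupported:
- That the plan contradicts its claimed strength. Strengths and Limitations says that the within-group comparison "will enable a comparison not subject to confounding by between-person variation". The full-sample model supplies that comparison, and the claim is not made for this subset.
- That the regression ignores people who appear under more than one method. The text says only that regression models will be used. Their handling of repeated persons may be in a plan not shown.
- That the methods will be ranked wrongly. With equal spread the order is kept on average.

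**Conclusion.** The point holds for this supplementary comparison. Selecting on the outcome is written into the plan and does not depend on any assumed figure, and the listed covariates cannot correct it. The size does depend on assumptions (normal ratios, chosen means and SDs) and on a tertile definition that the article leaves open. A gap of 0.10 may fall to about 0.03 or stay intact. With SDs of 0.15 and 0.25, a false gap of 0.08 (pooled) to 0.11 (within method) arises between methods with equal means. The order on mean bias can reverse under either cut.

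A reader might infer that the main accuracy result is compromised. It is not, because the full-sample mixed model keeps every eligible feeding day. The change is worth making because the test would be read at P<.05 and its result cannot be interpreted as a difference between methods.

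**What to change.** Make the between-method comparison of size of misestimation on all eligible feeding days, with the mixed model already planned (method and order as fixed effects, and participant stated as a random effect):
- for bias, the reported-to-observed ratio or its logarithm;
- for size of error, absolute percentage error, already named under Cost and Cost-effectiveness of Measures;
- if underreporting itself is of interest, the whole-sample shortfall max(0, observed − reported).

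Drop the underreporter-only between-method test, or keep the result as descriptive, with no between-method P value. If it is kept, state whether the tertile is pooled or within method.

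Cost: analysis wording only, with no change to data, visits or sample size. One planned supplementary test is lost.
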